### Genetic Analysis

This study will leverage a quality control and analysis pipeline established for the GP2 program. After standard quality control of raw genotyped data, data will be imputed to the most recent build of the multiethnic 1000 genomes reference panel using the default settings of miniMac2. This will yield ~15 million variants to test after additional quality control. These data will be contributed to GP2 for genome-wide association meta-analysis and admixture mapping. Within the RaDPD sample, ~90 currently established common PD risk variants to examine frequencies will be extracted. For analyses of PD genetic modifiers, linear regression—with an initial focus on outcome phenotypes with established evidence from the published literature, including age of onset, motor progression, and cognition—will be performed [59-65]. These outcomes will be supplemented with the most promising outcomes based on the results from aim 1 analyses identifying clinical features that differentiate PD in Black versus White patients. Sequencing results will be available for participants in PD GENEneration for 7 genes associated with PD: *GBA, LRRK2, PRKN, SNCA, PINK1,*
*PARK7,* and *VPS35*. Comprehensive genome sequencing of all samples is planned for a future project.

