### Objective

The overall objectives of this study are to perform comprehensive phenotyping, compare Black and White persons with PD, and investigate causes of racial disparities, including differences in clinical management and responsible genetic risk factors. The study is partnering with the ongoing Global PD Genetics Program (GP2) [19], which contributes samples and granular phenotypic data from the enrolled participants to enhance our understanding of the genetic architecture of PD in the Black population. The long-term goal of this application is to address the critical gap in knowledge of PD in this underserved population to improve diagnosis, optimize treatment, and plan for clinical trials. The central hypothesis is: PD is phenotypically and genetically different in Black versus White populations, and Black patients receive different and suboptimal clinical management. The research questions this study hopes to answer are as follows: (1) whether Black participants with PD have worse quantitative motor function and cognition, higher levels of depression and disability, and reduced quality of life compared with White participants with PD; (2) whether pharmacological, surgical, rehabilitation, mental health, and telehealth interventions differ by race with underuse of newer or more costly interventions in Black participants with PD; and (3) whether the contribution of genetic factors to PD risk and heterogeneity differs by race.

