### Study Setting and Design

The 7 study sites are Rush University, University of Maryland, University of Cincinnati, University of Pennsylvania, University of Chicago, Emory University, and Morehouse University (Figure 2). The sites were chosen based on US census data showing higher populations of Black persons in these geographic regions. A total of 400 Black patients with PD and 200 White patients with PD will be recruited. Patients who consent to enroll will have a single study visit encompassing data and sample collection for all 3 aims. A virtual option can also be used to complete questionnaires, followed by an in-person visit for the remaining measures.

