### Outcome Measures

The primary outcome measures to characterize PD phenotypes include the NIH Toolbox Motor assessments (2-minute walk, 4-meter walk, balance test, pegboard test, and grip strength) [28]; the Montreal Cognitive Assessment (MoCA), Symbol Digit Modalities Test (SDMT), PROMIS Profile-29 Physical Function, Parkinson’s Disease Questionnaire-8 (PDQ-8), and the MDS-UPDRS. The primary outcome measures to assess PD clinical management include the proportion of participants with antiparkinsonian medications prescribed at the initial visit to the neurologist, the proportion of participants with initial treatment of depression, and the proportion of participants with PD surgical interventions. To characterize genetic risk variants in our sample, the frequencies of the 90 established common PD genetic risk variants based on published genome-wide association studies in a predominantly White population will initially be examined. The study team will also aggregate and summarize sequencing results from PD GENEration, including potential rare variants among 7 established PD genes. The proportion of LRRK2- and GBA-PD will be summarized based on either PD GENEration, which permits comprehensive detection of potential pathogenic alleles, or GP2 genotyping, which can detect many of the most common, recurrent pathogenic variants. Finally, exploratory genotype–phenotype analyses will determine whether established PD risk variants modify clinical manifestations in Black individuals.

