### Sample Size

The sample size was calculated for each primary outcome measure described above with 80% power and a 2-sided test to detect a similar effect size observed from our pilot data (Table 4). Bonferroni correction was applied to control the overall significance level at .05. The minimal sample size for these analyses requires 365 Black and 183 White participants to complete this aim. The data observed in 3 studies guided the sample size calculation for PD clinical management (White vs non-White or Black: 78% vs 62% for measure 1 [4], 92% vs 80% for measure 2 [56], and 10% vs 0.4% for measure 3 [57]). The sample size was calculated using 90% power and a 2-sided test for each primary measure. Bonferroni correction was applied to control the overall significance level at .05. With a 1:2 ratio, the largest sample size required among all 3 measures is 173 White patients with PD and 346 Black patients with PD. For the genetic studies, our sample size will permit exploratory analyses, and all data will be contributed to GP2 for fully-powered meta-analysis.

**Table 4 table4:** Pilot data effect sizes for sample size calculation.

Primary measures	White patients with PD^a^ (n=25), mean (SD)	Black patients with PD (n=25), mean (SD)
4-meter walk computed score	1.1 (0.2)	0.8 (0.3)
Balance *t* test score	47 (12)	32.7 (13.1)
Pegboard dominant score	33.2 (10.9)	41.4 (15.6)
MoCA^b^	27 (2)	23.3 (3.1)
SDMT^c^	49.6 (9.1)	39.4 (14.1)
PDQ-39^d^	12.8 (7.9)	22.5 (12.3)

^a^PD: Parkinson disease.

^b^MoCA: Montreal Cognitive Assessment.

^c^SDMT: Symbol Digit Modalities Test.

^d^PDQ-39: Parkinson’s Disease Questionnaire.

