### Statistical Analysis

Each primary outcome measure will be compared between Black and White patients with PD. Bonferroni correction will be applied. The primary outcome measures are a 4-meter walk computed score, Balance test *t* score, Pegboard dominant *t* score, MDS-UPDRS motor score [26], MoCA [33], SDMT [58], PROMIS Profile-29 Physical Function, and PDQ-8 [46]. For significant measures, linear regression analysis will be performed to examine further the difference between the 2 groups with adjustment for age, sex, and disease duration. The interaction effects of race with these 3 variables will be explored. Regression analysis for cognitive measures will adjust for depression and anxiety scales in addition to these demographics. Regression will also be adjusted for comorbidities using the Cumulative Illness Rating Scale-Geriatrics score. The study site effect will be controlled as a random effect in the model. All analyses will be done using SAS (version 9.4).

For the PD management analysis, each primary outcome measure will be compared between Black PD and White PD groups using the chi-square test or Fisher exact test. Bonferroni correction will be applied. A hierarchical logistic regression analysis will assess the determinants of racial disparities in management. Besides race, age, sex, and education, income, symptom severity, and comorbidities will be included in the model. The interaction effect of race with those variables will be explored. The study site effect will be controlled as a random effect in the model. Secondary analyses will investigate differences between White PD and Black PD groups in other clinical management measures, including telehealth, participation in clinical trials, and rehabilitation therapy.

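### The Aim 3 genotype–phenotype analysis estimates variant effects in Black participants and contains no contrast by race, so it does not by itself address the heterogeneity part of research question 3

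*Protocol article*

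**What the plan says.** **The question.** The Objective section lists three research questions. The third is "whether the contribution of genetic factors to PD risk and heterogeneity differs by race". The Ethical Considerations section also describes the aim as a Black–White comparison of how genotype and phenotype relate.

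**The analysis.** Under Outcome Measures, "exploratory genotype–phenotype analyses will determine whether established PD risk variants modify clinical manifestations in Black individuals". The Genetic Analysis section gives the method: "For analyses of PD genetic modifiers, linear regression", starting with outcomes that have published support (age of onset, motor progression, cognition). Outcomes suggested by the "results from aim 1 analyses identifying clinical features that differentiate PD in Black versus White patients" are then added. The same section says that about "90 currently established common PD risk variants to examine frequencies will be extracted".

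**Status and size.** The Sample Size section says: "For the genetic studies, our sample size will permit exploratory analyses, and all data will be contributed to GP2 for fully-powered meta-analysis". Under Study Setting and Design, "A total of 400 Black patients with PD and 200 White patients with PD will be recruited".

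**Race interactions elsewhere.** In the Statistical Analysis section, the phenotype aim adjusts for age, sex and disease duration, and "The interaction effects of race with these 3 variables will be explored". A similar sentence covers the management aim. Neither involves genotype.

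**The concern.** For phenotypic heterogeneity, asking whether a genetic contribution differs by race needs a comparison of the two groups. The modifier analysis, as described, has a different null: that a variant has no effect on the phenotype among Black participants. That null is false whenever the variant acts in Black participants, whether or not it acts equally in White participants.

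One of the three research questions would then have no stated analysis for its effect-modification component. The article does report race interactions for the other two aims, yet states none for the aim whose question is about a difference by race. Without a stated contrast, a reader of the results has only association findings in Black participants to set against a question about differences.

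The point is confined to heterogeneity among cases. It does not concern disease risk.

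**Working it through.** The protocol gives no power, alpha or effect size for the genetic aim, so there is no figure to reproduce. The check is in two parts.

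**1. Question against analysis**

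| Section | Content | Null implied |
|---|---|---|
| Objective | Contribution differs by race | Equal contribution in the two groups |
| Outcome Measures | Variants modify manifestations in Black individuals | Zero slope in Black participants |
| Genetic Analysis | Linear regression; outcomes listed, no model terms | Zero slope |
| Statistical Analysis | Race interactions with clinical and demographic covariates | Not about genotype |

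No row supplies a contrast of variant effects between groups.

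**2. Size of the gap, for illustration**

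From the protocol: 400 Black and 200 White participants. Assumed: additive variant, residual SD 1, the same allele frequency p and the same per-allele effect β in both groups, two-sided 0.05 without multiplicity adjustment.

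Formulas:
- SE of a slope in a group of n: 1/√(n·2p(1−p))
- SE of the variant × race term: √(SE_Black² + SE_White²)
- Rejection probability ≈ Φ(β/SE − 1.96)

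Standard errors:
- p = 0.2: SE_Black = 1/√128 = 0.088; SE_White = 1/√64 = 0.125; interaction SE = 0.153
- p = 0.3: SE_Black = 1/√168 = 0.077; SE_White = 1/√84 = 0.109; interaction SE = 0.134

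Rejection rates when the effect is identical in both groups:

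| p | β (SD per allele) | Black-only test | White-only test | Significant in Black, not in White |
|---|---|---|---|---|
| 0.2 | 0.2 | 62% | 36% | 0.62 × 0.64 = 40% |
| 0.2 | 0.3 | 92% | 67% | 0.92 × 0.33 = 30% |
| 0.3 | 0.2 | 74% | 45% | 0.74 × 0.55 = 41% |
| 0.3 | 0.3 | 97% | 79% | 0.97 × 0.21 = 20% (21% unrounded) |

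The variant × race test rejects at its nominal 5% in all four rows, because the true difference is zero. A simulation at p = 0.3 and β = 0.3 (3000 data sets) gave 96.7% for the Black-only test and 4.6% for the interaction. With a smaller assumed effect of 0.1 SD, the Black-only test rejects in 20% (p = 0.2) to 25% (p = 0.3).

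**Precision of the missing contrast.** The 95% half-width for the difference in slopes is 1.96 × 0.134 = 0.26 SD at p = 0.3 and 1.96 × 0.153 = 0.30 SD at p = 0.2. Over those two frequencies, power to detect a true difference of 0.1 to 0.3 SD is 10% to 61% at 0.05. At 0.05/90, for about 90 variants, it is 0.3% to 11%.

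**The case against.** **The regression fits its own stated purpose.** A within-Black test has the right null for what Outcome Measures describes, the work is labelled exploratory, and the powered analysis is left to GP2. This stands as a limit on severity. It does not close the gap: an exploratory label concerns strength of evidence, not which contrast is estimated. The GP2 work named is genome-wide association meta-analysis and admixture mapping, with no comparison of modifier effects by race described.

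**Contribution is more than a per-allele effect.** This stands. A variant's contribution to variance is roughly 2p(1−p)β². With β = 0.3 in both groups and assumed frequencies of 0.2 and 0.5, it is 0.32 × 0.09 = 0.029 against 0.50 × 0.09 = 0.045, although the interaction is zero. The planned frequency work is therefore part of the answer, and an interaction term alone would not be the whole of it. But frequencies cannot show whether a variant acts differently.

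**A condensed article may leave model terms to the full protocol.** This is fair for covariates. Here, though, the article states a question about both groups and an analytic target in one.

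**Stronger readings that the text does not support.**
- A reader might infer that the study would answer question 3 yes whenever a variant is significant. No rule links a coefficient to that answer, nor does the protocol propose reading significance in one group only as a difference.
- A reader might infer that the White participants serve no purpose. The stated sample size requirements come from the phenotype and management aims (183 and 173 White participants), and White genotypes can still inform frequency comparisons and GP2.
- A reader might picture a pooled regression without race, confounded by allele frequency. Outcome Measures points to Black individuals, so that model is not what is described.

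**Conclusion.** The point holds in a limited form. As described, the genotype–phenotype analysis estimates association in Black participants and does not by itself address whether variant effects on the phenotype differ by race. Under the assumed equal effects of 0.2 to 0.3 SD per allele and frequencies of 0.2 to 0.3, a Black-only test rejects about 62% to 97% of the time, against about 5% for a variant × race test. The gap narrows with smaller effects or a stricter alpha. The mismatch between question and contrast does not depend on these assumptions, since it follows from the text. It does not show that the study would reach a wrong answer to question 3. It is worth correcting, in proportion to an aim declared exploratory.

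**What to change.** Either of two changes resolves it.

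**Add the contrast.** For each modifier outcome, fit an exploratory model in all genotyped participants with variant (or risk score), race, variant × race, genetic-ancestry components and sex, plus age and disease duration where suitable. Do not adjust age of onset for both: if duration is counted from onset, onset equals age minus duration and the model is degenerate. Report the variant × race estimate with its confidence interval, beside the Black-specific slope and the allele-frequency comparison. State that a difference by race will not be inferred from significance in one group only.

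**Or narrow the question.** Restrict the heterogeneity part of research question 3 to variant effects in Black participants, and state that differences by race are left to GP2.

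The first option adds an exploratory model per outcome on data already planned, with no change to recruitment or visits. Its drawback is imprecision at 400 and 200, so it should be presented as exploratory estimation. The second option costs only wording, but gives up this part of the question within the study.

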### Ethical Considerations

This study was approved by the Rush Institutional Review Board (IRB; ORA 20121005), which serves as the single-site IRB for this study. Each participant will sign a consent form, which includes blood and genetic analysis, before participation. Each participant also signs permission for the DNA results from sequencing to be housed in the PDGeneration database and the National Institutes of Health (deidentified) through GP2. If the participant requests genetic results, they are identifiable to PDGeneration, facilitating the return of results. Potentially vulnerable study populations are patients with cognitive impairment and socioeconomic disadvantages. Given the study aims to investigate racial disparities in the phenotype–genotype differences between Black and White patients with PD, it is necessary to include these populations. Study participants must be able to provide informed consent as determined by the Evaluation to Sign Consent to confirm they understand the risks and benefits and can provide their informed consent. This low-risk study does not present a greater risk to potentially vulnerable populations. Given the short duration of this study (1 study visit), it is not expected that significant cognitive decline will occur throughout the study to impact a participant’s ability to provide ongoing consent. Participants unable to achieve a passing score on the Evaluation to Sign Consent will be excluded unless a LAR is present to provide consent.

A human subjects research ethics review will occur at the time of IRB approval. The informed consent process occurs with the study team live during the study visit. Data are entered directly into a password-protected, Health Insurance Portability and Accountability Act–compliant REDCaP database, with the participant having an assigned site-specific study ID. Participants are compensated US $100 for the study visit plus US $25 for travel expenses, and some sites arrange transportation with established institutional programs.

## Results

The Rush IRB approved the project as the single-site IRB in February 2022 and funded by NINDS in April 2022. Recruitment began in July 2022. At the time of submission of this manuscript, 131 participants had been enrolled. One of the original study sites has been replaced by a new site due to issues with regulatory approval. Other activities have included quarterly steering committee and monthly coordinator meetings. Steering committee meetings include discussing recent publications and speakers focused on racial disparities.

## Discussion

### Study Rationale

The study rationale is that the knowledge gained will improve clinical diagnosis and management for Black persons with PD, drive programming to improve access to care and management, and inform research strategies in PD in the Black community. It is anticipated that the main findings of this study will be that Black patients with PD will have more gait abnormalities and higher rates of genetic variants for PD specifically seen in the Black population. It is also anticipated that Black individuals with PD will be less likely to have been referred or have access to specialized care for PD, including surgical treatments and nonmedication therapies. This protocol was structured as a one-time visit to encourage participation and to optimize the likelihood of full data collection. Aim 3 is a collaborative effort with the Global Parkinson’s Genetics Program (GP2), a worldwide consortium funded by the Aligning Science Across Parkinson’s initiative to understand the genetic architecture of PD. This collaboration enables samples collected in this study to be part of a larger gene discovery effort with investigators from African and Afro-Caribbean patients with PD to foster a greater understanding of genetic variation specific to the Black population [17]. This study fills a unique niche by performing deep phenotyping to study racial disparities and analyze genotype–phenotype relationships in PD.

The recruitment of Black patients into research studies is historically much lower than White patients [22]. Contributory factors include distrust owing to historical research abuse and institutional racism, lack of information and understanding of research studies and informed consent, insufficient recruitment efforts by researchers, social stigma, and financial considerations [66]. In 1993, the National Institutes of Health established the Revitalization Act, which mandated minority inclusion in randomized clinical trials. An important strategy to promote study recruitment in both Black and White patients with PD is raising awareness of previous studies showing evidence of racial disparities in access to care, disease features, and clinical management.

A potential barrier to participation in PD research is motor and cognitive impairments, present in patients with PD of all racial and ethnic backgrounds. To accommodate the needs of patients with more severe motor and cognitive impairment, the protocol was designed to allow for the collection of a “minimum dataset.” The goal is to complete as many study assessments as possible. However, implementing more limited data collection will enable the successful completion of enrollment targets and ensure the inclusion of a representative range of disease severity. The typical time of the study visit is between 3 to 6 hours, and more limited data collection, focused on the primary outcome measures for each of the study aims, reduces the visit time to 1 to 2 hours.

### Conclusions

Many unique challenges arise in clinical research in the Black PD community, but the importance of understanding racial disparities warrants focus on this population. Given what little is known about how PD manifests in Black patients, this will be the most comprehensive study of the phenotype and management of PD in the US Black population, with the potential to improve clinical diagnosis and management and to foster future research directions. It is not clear what the true implications of the study will be, but improvement of study recruitment in this population, education of patients, caregivers, and clinicians on disparities, and ultimately, changes in practice will drive the final impact of the study and drive health policy recommendations at a national level.

## Appendix

Multimedia Appendix 1 Instruments, measures, and scale information.

Multimedia Appendix 2 Peer-review report from the Clinical Neuroscience and Neurodegeneration Study Section (CNN) - Brain Disorders and Clinical Neuroscience Integrated Review Group - Center for Scientific Review (National Institutes of Health, USA).

